## Abstract

**Background:**

Non-invasive neuromodulation (NIN) techniques have been widely utilized in treating patients with disorders of consciousness (DoC), but their therapeutic effects have been inconsistent. Given the reliance of NIN techniques on synaptic plasticity, and the potential impairment of synaptic plasticity (particularly homeostatic plasticity) resulting from severe brain injury, it is possible that the variation in therapeutic effects is due to alterations in homeostatic plasticity in patients with DoC. Therefore, this study will use preconditioning TMS to examine the retention of homeostatic plasticity in patients with DoC.

**Methods:**

We will enroll 30 patients with DoC and 15 healthy controls and randomize the order of their sessions. According to the priming protocol, the trial was divided into three different sessions with a 2-day break between each session. The session will involve a 10-min duration of transcranial direct current stimulation (tDCS) priming, followed by a 192-s period of transcranial magnetic stimulation (TMS) test. Transcranial stimulation will be specifically targeted toward the left primary motor cortex. Measurements of motor evoked potentials will be taken at several time points: baseline, after tDCS, and after TMS. Coma Recovery Scale-Revised will be conducted both baseline and after TMS.

**Discussion:**

Studying whether homeostatic plasticity is preserved in patients with DoC is beneficial for gaining a better understanding of their brain condition. If the homeostatic plasticity of patients with DoC is impaired, then NIN, which are based on altering synaptic plasticity in healthy individuals to achieve stimulating effects, may not be directly translatable to the therapeutic interventions for patients with DoC. Instead, the homeostatic plasticity of patients should be restored before implementing the intervention.

## Introduction

1

Consciousness, which consists of arousal and awareness, is the subjective projection of the human brain onto the objective world. When the brain is subjected to ischemia, hypoxia, external impact and other brain damage, there may be a loss of consciousness, and severe brain damage can even lead to disorders of consciousness (DoC) (1). Following brain injury, some patients may enter a state of coma characterized by a lack of both arousal and awareness (2). Unresponsive wakefulness syndrome (UWS) (3) is diagnosed when the patient recovers from a coma and reappears the sleep–wake cycle, but only shows reflexive movements and still has no awareness. Some patients may further transition to minimally conscious state (MCS), during which they exhibit some intentional behaviors. This manifestation of consciousness is fluctuating yet replicable (4). When patients improve further on the basis of MCS, they are thought to no longer have consciousness disorders, but mainly motor and cognitive impairment.

As an extremely disabled group, DoC patients impose a significant burden on their families and society. To address this challenge, various treatments have been proposed for these patients, with non-invasive neuromodulation (NIN) technology, such as transcranial direct current stimulation (tDCS) and transcranial magnetic stimulation (TMS), emerging as a standout option. These methods are portable, bedside-friendly, and capable of modulating brain activity. However, their efficacy remains inconsistent. While some studies demonstrate positive outcomes (5, 6), a recent trials have questioned the effectiveness of tDCS (7). Moreover, many NIN interventions produce mixed results, possibly due to the failure to account for the impact of the pre-treatment brain state, such as homeostatic plasticity, on the efficacy of NIN (8).

Although the mechanisms underlying NIN remain unclear, current research indicates that these stimuli affect neuronal activity by influencing synaptic plasticity, thereby adjusting the excitability of the cerebral cortex (9). Synaptic plasticity can be further categorized into Hebbian plasticity with positive feedback and homeostatic plasticity with negative feedback (10). Hebbian plasticity can specifically modify synapses to enhance [Long-term Potentiation (LTP)] or weaken [Long-term Depression (LTD)] synaptic transmission (11), a process thought to underlie the neurophysiology of learning and memory (12). However, this positive feedback mechanism can result in over-excitation or over-inhibition in the human body (13). Hence, a balancing homeostatic mechanism in the human body regulates Hebbian plasticity by stabilizing neuronal activity. This homeostatic plasticity counteracts the destabilizing effects of Hebbian plasticity, keeping neural activity within a physiologically significant range (14, 15).

Homeostatic plasticity can happen through two mechanisms: the sliding threshold theory (16) and the synaptic scaling theory (17). As per the sliding threshold theory, synaptic activity can modify the connection between synaptic input and neuron firing by adjusting a sliding threshold. Lower postsynaptic activity decreases the threshold for triggering LTP, increasing the likelihood of generating excitatory responses in synapses. In contrast, higher postsynaptic activity raises the threshold for LTP induction, encouraging the production of inhibitory responses. The synaptic scaling theory regulates neuronal activity by directly adjusting synaptic strength, either up or down. In a long-term LTD-like environment, excitatory synapses and Na ion channels increase, facilitating neuron excitation. Conversely, in a long-term LTP-like environment, inhibitory synapses and K ion channels increase, hindering excitatory responses. These mechanisms help maintain the overall activity of the neuronal network within a suitable range, preventing excessive excitation or inhibition.

Given the negative feedback mechanism of homeostatic plasticity, we can propose a priming-test preconditioning TMS tool that is more effective than the current stimulation alone. Initially, subjects will receive inhibitory priming to trigger their homeostasis response, followed by an excitatory test. As a result of the preceding inhibitory treatment, the neural network near the subject’s target area will more readily generate an excitatory response, leading to a more significant neural network activity during the excitatory test compared to the excitatory stimulus alone. Homeostatic plasticity plays a critical role in maintaining neural stability; thus, its impairment could limit the efficacy of NIN interventions. Research on myasthenia gravis (18), dystonia (19–21), Parkinson’s disease (22), Alzheimer’s disease (23), depression (24) and other psychiatric disorders (25) have highlighted deficiencies in homeostatic plasticity among patients, raising concerns about its preservation in DoC patients.

Therefore, prior to administering the combined stimulation to DoC patients, it is crucial to investigate the preservation of homeostatic plasticity in these individuals. This study is guided by two hypotheses: firstly, that DoC patients exhibit impaired homeostatic plasticity, with the degree of impairment correlated with their level of consciousness; and secondly, that patients who retain homeostatic plasticity may have a more favorable prognosis. To explore the retention of homeostatic plasticity in DoC patients, this study will employ two NIN technologies, tDCS and TMS, as assessment tools.

## Methods

2

### Design

2.1

We design a prospective, randomized, double-blind, repeated-measures crossover experiment to explore the preservation of homeostatic plasticity in patients with DoC. This study is registered in the Chinese Clinical Trial Registry (ChiCTR2300077784^1^), and protocol is aligned with the Declaration of Helsinki, approved by the Science Research Ethics Committee at the School of Basic Medicine, Hangzhou Normal University (20231024).

### Participants

2.2

This study will include 15 patients with MCS, 15 patients with UWS, and 15 healthy subjects sourced from various hospitals. Before enrollment, each DoC patient will undergo five assessments using the Coma Recovery Scale-Revised (CRS-R) over a 10-day period conducted by assessment experts. The best result from the five assessments will be considered as the patient’s current level of consciousness, and assessment experts will assess if the patient meets the inclusion criteria during the evaluation process.

The criteria for inclusion and exclusion are outlined in Table 1.

**Table 1 tab1:** Inclusion and exclusion criteria.

Inclusion criteria	Exclusion criteria
Diagnosed in DoC with 5 times CRS-R assessments;	Active seizures or a history of mental illness;
Disease onset more than 28 day;	Metal implants in the skull;
Intact skin and anatomical structure;	Lack of motor evoked potential from right first dorsal interosseous muscle;
Right-handed as per Edinburgh Handedness Inventory;	Unstable vital signs;
Stable central nervous system drug therapy for 1 week before enrollment.	Use sedatives, sodium or calcium channel blockers.

DoC, disorders of consciousness; CRS-R, Coma Recovery Scale-Revised.

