In this study, tDCS and TMS will be used to detect homeostatic plasticity retention in patients with DoC. tDCS applies low-amplitude (1–2 mA) direct current to the brain via two scalp electrodes, modulating the threshold of action potential generation, thereby depolarizing (anode) or hyperpolarizing (cathode) individual neurons (9, 44, 45). TMS is a technique that integrates nerve stimulation and cortical excitability detection. It uses electromagnetic induction to induce secondary currents in subcortical neurons, thereby activating neurons to change physiological processes in the brain (46, 47).

While two NTBS technologies, tDCS and TMS, are widely used in the field of treatment for DoC, the selection of parameter and targets often relies on studies related to other diseases or healthy individuals. In DOC, the most common targets are the M1 or the dorsolateral prefrontal cortex (DLPFC) rather than the anterior cingulate cortex or posterior cingulate gyrus emphasized by many theories of consciousness. M1 is frequently targeted in the motor rehabilitation of stroke patients, while DLPFC is primarily employed in depression treatment (48). Such empirical transplantation carries significant theoretical risks—severe brain injury may fundamentally alter homeostatic plasticity mechanisms, and directly applying neuromodulation parameters from healthy populations may lead to diminished efficacy or even induce secondary damages such as epilepsy.

Based on these findings, we propose a stepwise intervention strategy. The primary task is to assess the retention of homeostatic plasticity in DoC patients. For patients with impaired homeostatic plasticity, priority should be given to restoring this mechanism before proceeding with neuromodulation treatments to prevent uncontrolled risks caused by impaired negative feedback regulation. Previous successes in dopamine modulation for Parkinson’s disease (22) suggest that the neurotransmitter system may serve as an important regulatory target. In some cases, impaired homeostatic plasticity might even indicate the irreversibility of a patient’s condition.

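### Table 1 excludes prior mental illness but not the four neurological diseases that the article itself links to deficient homeostatic plasticity, which leaves a modest, one-sided possible confounder

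*Protocol article*

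**What the plan says.** Section 2.2 (Participants) states that "The criteria for inclusion and exclusion are outlined in Table 1". The only line in that table on prior or current disease as such is "Active seizures or a history of mental illness". The other exclusions concern metal in the skull, a missing motor evoked potential (MEP) from the right first dorsal interosseous muscle, unstable vital signs, and the use of sedatives or of sodium or calcium channel blockers.

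The Introduction names myasthenia gravis, dystonia, Parkinson's disease, Alzheimer's disease, depression and other psychiatric disorders. It says that studies of them "have highlighted deficiencies in homeostatic plasticity among patients, raising concerns about its preservation in DoC patients". The first hypothesis, in the same section, is that "DoC patients exhibit impaired homeostatic plasticity, with the degree of impairment correlated with their level of consciousness". The Abstract gives the suspected origin as "the potential impairment of synaptic plasticity (particularly homeostatic plasticity) resulting from severe brain injury".

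Section 2.11 makes the comparison of healthy individuals with DoC patients the primary focus, using the course of normalized MEP under each priming type.

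**The concern.** Table 1 deals with the psychiatric part of the Introduction's list and is silent on the neurological part. By the article's own citations, a patient with pre-injury Parkinson's disease, for example, might respond abnormally to priming even without a brain injury. Such a patient can be enrolled as a DoC case but, on the ordinary meaning of the word, not as a healthy control. The omission therefore acts on one side of the primary comparison.

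At stake is the attribution. A deficit in the DoC groups is to be read as a feature of DoC, and part of it could belong to an earlier disease or to the drugs given for it. The same patients would enter the comparisons of preserved homeostatic plasticity between MCS and UWS and between good and poor prognosis, and the planned correlations.

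**Working it through.** **Step 1. Does another provision close the gap?** Each candidate was set against a patient with one of the four diseases before the injury.

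| Provision | Removes or adjusts for such a patient? |
|---|---|
| Mental illness or active seizures (Table 1) | Not by its wording; none of the four diseases is named |
| Missing MEP; sedatives or channel blockers (Table 1) | Only by chance; the disease is not the target |
| Intact skin and anatomy (Table 1); T1 scan of M1 (section 2.9) | No; these concern structure, not diagnosis |
| CNS drugs stable for 1 week (Table 1) | No; a patient on unchanged long-term drugs meets it |
| Subgroups and tests (section 2.11) | No; patients are grouped by consciousness level and prognosis only, with no stated adjustment for earlier disease |

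**Step 2. Does the crossover protect the comparison?** No. Each patient is his or her own control across anodal, cathodal and sham priming. A lack of homeostatic response caused by earlier disease would show as no difference between priming types within that patient. Impairment due to DoC would look the same.

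**Step 3. How large could it be?** The plan states no figure to reproduce. Its inputs are 30 DoC patients (15 MCS, 15 UWS) and 15 controls (section 2.2), and a 20% data loss rate (section 2.3), which leaves 15 × 0.8 = 12 per group. The share p of affected patients is assumed to be 2%, 5% or 10%.

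Let R be the mean priming response of unaffected patients, and let affected patients have a response of 0. The expected DoC mean is (1 − p) × R + p × 0, so the expected reduction is p × R.

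| Assumed p | Expected number, 30p | Chance of at least one, 1 − (1 − p)^30 | Expected reduction in DoC mean |
|---|---|---|---|
| 2% | 0.6 | 45% | 2% |
| 5% | 1.5 | 79% | 5% |
| 10% | 3.0 | 96% | 10% |

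The last column measures the bias. The chance of at least one affected patient shows only how likely the situation is to arise.

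If the other DoC patients are impaired as well, R is below the healthy response and the added shift shrinks with it. For example, if R is half the healthy response, the shift is 1%, 2.5% or 5% of the healthy response.

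One affected patient lowers the mean of all 30 by 1/30 = 3.3%. It lowers the mean of the MCS or UWS group that contains the patient by 1/15 = 6.7%, or by 1/12 = 8.3% with 12 evaluable. The other group does not move.

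**Step 4. Against sampling error.** The documents give no standard deviation (SD). If the between-patient SD equals the mean response, the standard error of a 30 versus 15 comparison is √(1/30 + 1/15) = √0.10 = 0.32 of that mean. The shift is then 0.02/0.32 to 0.10/0.32, or about 0.06 to 0.32 standard errors. With an SD half as large, the standard error is 0.16 and the shift about 0.13 to 0.63 standard errors. On these assumptions it stays below one standard error.

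**The case against.** **This is a condensed article, and the fuller protocol may hold more exclusions.** That is possible. But the article does set out its eligibility criteria, and the point concerns what those criteria admit, so it is more than detail left out for space.

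**There is no contradiction.** This stands. The Introduction cites the diseases to motivate the question and commits to excluding none of them. A reader might infer that Table 1 was meant as an exclusion list based on plasticity and was left half finished. The documents do not support that: mental illness is paired with active seizures and no reason is given. Mental illness is also undefined, so it is not certain that dementia falls outside it.

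**The aim is to learn whether plasticity is retained, whatever the cause.** This stands in part. For deciding whether a patient is suited to neuromodulation, and for the prognostic hypothesis, the origin of a deficit may not matter, and excluding these patients narrows the population. But the Abstract ties the suspected impairment to the brain injury, and the primary contrast is with healthy people. For that claim the origin does matter.

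**Affected patients need not push the result towards the first hypothesis.** This stands for treated patients. The Discussion reports that successes with dopamine modulation in Parkinson's disease "suggest that the neurotransmitter system may serve as an important regulatory target", so drug treatment may partly restore the response. The response would then reflect the earlier disease and its treatment, with no certain direction.

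**The four names come from an illustrative list.** This stands too. The documents do not show that the list is complete or that these are the comorbidities that matter most here.

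**Conclusion.** The gap is real. The stated criteria admit to the DoC groups, and in effect only there, patients with earlier diseases that the article itself associates with the deficit under study. No stated criterion or analysis removes or separates them.

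Its size is modest. With an assumed 2%, 5% or 10% of patients affected, no response in them and a normal response in the rest, the expected reduction in the DoC mean response is 2%, 5% or 10%. It is less if the rest are impaired, and it may be zero if no such patient is enrolled.

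Two stronger conclusions are tempting. One is that the first hypothesis would be wrongly confirmed. The documents give no prevalence, age range or SD from which to show that, and under the assumed SDs the shift is well under one standard error. The other is that the links with consciousness level and prognosis would be inflated. That would require these diseases to go with lower consciousness or worse recovery in this sample, and nothing in the documents says that they do. The point is therefore a cheap improvement to the design and leaves the study's rationale intact.

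**What to change.** Add to the exclusions in Table 1 a pre-injury diagnosis of Parkinson's disease, Alzheimer's disease, dystonia or myasthenia gravis, checked from the medical history for patients and controls alike. Limit it to diagnoses made before the injury, so that signs caused by the injury itself do not exclude a patient. For anyone already enrolled, repeat the primary comparison without participants who have such a diagnosis and report both results.

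The cost is one line in the table, a check of the history, and one sensitivity analysis if affected participants are already in the study. The downside is the loss of a few, mainly older, candidates and a slightly narrower population.

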### Sample size

2.3

The sample size calculations had been performed using G*power 3.1 (26) with prior power analysis. Based on previous studies of DoC patients (27), the effect size f had been calculated to be 0.3. A three-way repeated measures ANOVA had been conducted with test power (1-*β*) set at 80% and the type I error rate (*α*) of 5%. Taking into account an allocation ratio of 1:1:1 and a 20% data loss rate, this had resulted in a minimum of 15 participants per group.

### Procedures

2.4

The study process will begin as early as 28 days after the patient’s injury, and the entire experimental process will be finished within 10 days. After informing the patient’s legal representative about the experimental content and potential adverse reactions, written informed consent will be obtained from them. They will be advised that they can choose to exit the study at any time without the requirement for providing a reason. After informing the healthy subjects of the experimental content and potential adverse reactions, they will sign the informed consent form.

Before the trial, DoC patients will have the option to undergo a functional magnetic resonance imaging (fMRI) scan, and they can choose to decline. Over a period of 10 days, five CRS-R assessments, and an fMRI scan will be completed. The study protocol is a repeated-measures crossover design. According to different tDCS priming protocols (anode, cathode, sham), the trial will be divided into three distinct sessions. Each session will involve 10 min of tDCS priming followed by 192 s of TMS test, with both transcranial stimulations specifically targeted toward the left M1. We will measure the motor evoked potential (MEP) amplitude at four time points: baseline (PRE), after tDCS (INTER), and at 5 and 15 min following TMS (POST-1, POST-2). CRS-R data will be collected at baseline (PRE) and 20 min after TMS (POST-3). Upon enrollment, participants will receive a serial number based on their order of enrollment, with each serial number corresponding to a randomly generated session order. Subjects will then undergo three sessions following the designated session order, with a two-day washout period between each session. The entire trial will be completed in 5 days. Patient prognostic data will be gathered at 3, 6, and 12 months after the conclusion of the study. Figure 1 provides a detailed illustration of the study flow.

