### Statistical analysis

2.11

A single transcranial stimulation typically leads to limited behavioral improvement but increases cortical excitability due to its immediate effects (36). Therefore, the primary focus of this study will be to analyze the trend of MEP changes over time in different priming types, comparing healthy individuals with DoC patients. At the individual level, the cathodal tDCS group will be compared with the sham group. The primary outcome of this study will be MEP, a measure used to assess neurophysiological changes. Since the baseline MEP in each session will be influenced by various factors such as the individual’s daily state, MEP data from different sessions will lack comparability. Therefore, all MEP data will be normalized in this study (normalized MEP = MEP/MEP baseline). The normalized MEP data will be subjected to an analysis of variance (ANOVA) to explore the retention of homeostatic plasticity in DoC patients and to determine whether the combination of cathodal tDCS and iTBS is superior to iTBS alone.

While a single stimulus may not directly lead to a change in behavior, this study will conduct a CRS-R assessment (specific item) before and after each session to ensure that any potential improvements are not overlooked. Homeostatic plasticity, as a fundamental characteristic of synapses, can impact a range of synaptic activities and may even influence levels of consciousness and prognosis. Therefore, the CRS-R score, which assesses the level of consciousness, will be considered as a secondary outcome of this study.

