Patients will be categorized into subgroups based on consciousness levels and prognosis. For consciousness levels, patients will be classified into the MCS or UWS group based on the best result from five baseline CRS-R assessments, To classify a CRS-R record as reflecting MCS, the participant must achieve at least one of the following criteria: a score of 1 on the communication subscale (intentional but non-functional yes/no communication), a score of 3 or higher on the auditory subscale (command-following), a score of 2 or higher on the visual subscale (visual fixation or better), a score of 3 or higher on the motor subscale (localization to noxious stimulation or better), or a score of 3 on the oromotor/verbal subscale (intelligible verbalization). If none of these criteria are met, the CRS-R record will be classified as reflecting UWS (37). For prognosis, patients will be evaluated at 3, 6, and 12 months, with those showing an increase of over 11 Rasch units (approximately 4–6 CRS-R points) (38) classified as the good prognosis group, while others will be placed in the poor prognosis group. A preserved homeostatic plasticity response is defined as a significant modulation of MEP amplitude following the priming-test protocol, consistent with the sliding threshold theory of synaptic plasticity. Its preservation was further compared between the MCS and UWS groups, as well as between the good and poor prognosis groups.

In this study, statistical analysis will be conducted using IBM SPSS Statistics 26 software. The collected data will first undergo normal distribution testing via Kolmogorov–Smirnov tests. If the data meets the criteria for a normal distribution, a three-way repeated measures ANOVA will then be carried out. However, if the data does not adhere to a normal distribution, Friedman’s ANOVA will be utilized instead. Following a significant outcome from the ANOVA, two-way ANOVAs will be conducted within each group to explore temporal changes in mean MEP amplitude. Additionally, Pearson correlation will be used to examine the relationship between homeostatic plasticity retention, consciousness, and prognosis. A significance level of *p* < 0.05 will be employed for determining statistical significance.

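### The planned ANOVA for this three-session crossover has no session-position (period) term, so any change in response across sessions goes into the error and costs precision

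*Protocol article*

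**What the plan says.** Section 2.1 (Design) describes a "prospective, randomized, double-blind, repeated-measures crossover experiment". Section 2.2 (Participants) sets the groups: "This study will include 15 patients with MCS, 15 patients with UWS, and 15 healthy subjects". Section 2.4 (Procedures) defines the sessions by the priming given: "According to different tDCS priming protocols (anode, cathode, sham), the trial will be divided into three distinct sessions". Three conditions give six possible orders.

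On allocation, section 2.4 says that "participants will receive a serial number based on their order of enrollment", with "each serial number corresponding to a randomly generated session order". It names no block, Latin square or stratum. Sessions are separated "with a two-day washout period between each session", and the same paragraph has the whole trial finished in 5 days.

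Section 2.11 (Statistical analysis) holds that "MEP data from different sessions will lack comparability", and therefore divides each MEP by the baseline of its own session. If the data pass a normality test, "a three-way repeated measures ANOVA will then be carried out". Two-way ANOVAs within each group follow a significant result. Friedman's ANOVA is the fallback.

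**The concern.** Dropping group from the three-way model leaves a two-way model within each group. The three factors are therefore group, priming and time (time point within a session). Neither session position nor sequence is a factor, and the Friedman fallback has no place for either.

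Each participant receives iTBS over the same left M1 site in three closely spaced sessions. The introduction rests on the idea that earlier synaptic activity changes the response to later stimulation, so a change in response across sessions is plausible. If it occurs, the model leaves it in the error. If orders are also not balanced within groups, the realised trial can place cathodal sessions earlier or later than sham sessions, and by different amounts in different groups. The contrasts affected are cathodal versus sham and group by priming, which are the ones the study is built on.

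**Working it through.** **Inputs from the article.** Three priming conditions (section 2.4); 15 per group (sections 2.2 and 2.3); cathodal versus sham as a named comparison (section 2.11). The article gives no period effect, so there is no figure of its own to reproduce on this point. The 15 per group is taken as given. It can be matched (within-between interaction, f = 0.3, three measurements, correlation 0.3: N = 36, and 36/0.8 = 45), but the correlation and number of measurements are not stated. Nothing below depends on that match.

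**Step 1: chance imbalance, if orders are simple random draws.** Let d be the position of the cathodal session minus that of the sham session. Over the six orders d is ±1 in four and ±2 in two, so its mean is 0 and its variance is (4×1 + 2×4)/6 = 2.
- One group of 15: SD of mean d = √(2/15) = 0.37 sessions. In simulation the absolute value is at least 0.5 in 17% of groups, and its 95th percentile is 0.73.
- Difference between two groups of 15: SD = √(2/15 + 2/15) = 0.52. It is at least 0.5 in 33% of trials, and its 95th percentile is 1.0.
- Healthy controls against all patients (15 versus 30): SD = √(2/15 + 2/30) = 0.45. It is at least 0.5 in 28% of trials.

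If instead one list across all 45 participants used permuted blocks of six, with groups arriving at random, the within-group SD falls to 0.30 but the between-group SD stays at 0.52. Only balance within each group protects the between-group comparison.

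**Step 2: what the imbalance does.** Shift in a contrast = imbalance × period effect g, in SDs of the paired difference per session. At the 95th percentile:

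| g | one group | two groups of 15 |
|---|---|---|
| 0.25 | 0.73 × 0.25 = 0.18 SD | 1.0 × 0.25 = 0.25 SD |
| 0.5 | 0.73 × 0.5 = 0.37 SD | 1.0 × 0.5 = 0.50 SD |

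These shifts are as likely to go one way as the other.

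**Step 3: power of the paired cathodal–sham contrast.** Assumptions: n = 15, SD of the paired difference 1, linear period effect g, true difference 0.78 (which gives 80% power at g = 0), two-sided 5%. With no period term and random order, the variance of the difference is 1 + 2g²: 1.125 at g = 0.25 and 1.5 at g = 0.5. The standard error is √(1.125/15) = 0.274 or √(1.5/15) = 0.316, against √(1/15) = 0.258 at g = 0. Simulation (8,000 trials per scenario, linear period term) gives:

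| g | random order, no term | random order, term | blocked order, no term | blocked order, term |
|---|---|---|---|---|
| 0 | 80% | – | – | – |
| 0.25 | 76% | 77% | 76% | 79% |
| 0.5 | 62% | 77% | 65% | 80% |

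In the random-order, no-term case the mean estimate stays at the true value, and type I error is 5.0–5.2% at g = 0.25 and 0.5. A fitted linear term removes g from the estimate, so power with the term does not depend on g. At g = 0 the term therefore costs about 3 points with random order (80% to 77%) and about 1 point or less with blocked order.

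**Step 4: spacing.** Three sessions fit into 5 days only on days 1, 3 and 5, which leaves one full day between sessions. Two full days between sessions would need days 1, 4 and 7. The two statements must be reconciled, because the interval bears on carry-over.

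**The case against.** The strongest reply has four parts.

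- **The lists may already be balanced.** A randomly generated order can come from a blocked or group-specific list. An article commonly leaves list construction to the full protocol, and the flow figure is not available here. This stands: a reader might infer that orders are unbalanced, but the text is only silent. The figures in Step 1 are conditional on simple random draws.
- **There is no bias.** A reader might also infer that the priming contrasts are biased or the error rate inflated. Neither follows. Random order makes the expected imbalance zero, and type I error stays near 5%. The harm is chance imbalance and lost precision.
- **Normalization already deals with session differences.** In part it does: dividing by the session's own baseline removes a multiplicative shift in MEP for that session. It does not remove a period or carry-over effect on the response to stimulation, which is the outcome analysed. Raw baselines are still recorded and can be inspected.
- **The loss may be small, and a nuisance term may sit in an analysis plan not shown.** At 0.25 SD per session, with orders left unbalanced, the term gains about one point of power; at zero there is nothing to gain. No size of period effect can be taken from the article. But the article does state its primary model and follow-ups, and session position has no place in them.

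**Conclusion.** The point holds as one of precision. The stated primary model for a three-session crossover omits session position, although the data to include it are recorded anyway. Under the Step 3 assumptions, the loss of power at n = 15 runs from none (no period effect) through 80% to 76% (0.25 SD per session) to 80% to 62% (0.5 SD per session). The period term does most of the repair: at 0.5 SD, blocked order alone reaches 65%, the term alone 77%, and both together 80%. The period effects are assumptions, the power figures are for one group's paired contrast rather than the full ANOVA, and the imbalance figures assume unrestricted random orders. The documents do not support a claim of systematic bias or of a known defect in the allocation list.

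**What to change.** 1. Add session position as a fixed effect, for example in a mixed model with group, priming, time and period, and state this before unblinding. Cost: about 2 df with position as a three-level factor, and no new data. If there is no period effect the price is a few points of power at most, and less when orders are balanced. The Friedman fallback cannot carry the term, so the alternative for non-normal data needs to allow for it as well.
2. Compare raw baseline MEP by session position and by preceding priming, as a descriptive check for carry-over.
3. State how the order list is built. If it is not already balanced within HC, MCS and UWS, balance session position within each group for participants not yet enrolled. Blocks of six do not divide 15, but Latin-square triplets do. A single cyclic square would fix which condition precedes which, so use both squares: three triplets from one and two from the other give three orders used three times and three used twice (3×3 + 3×2 = 15). Cost: new lists, with no burden on participants.
4. Reconcile the two-day washout with completion in 5 days.
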